**Summary**

Loss of a lower limb due to diabetes can have a devastating impact on physical and mental health and quality of life. Individuals are at risk of other diseases such as cardiovascular disease, loss of the other limb and death. Physical activity can reduce risk of chronic disease and improve health outcomes; however, physical activity levels in people with limb loss are low, often due to reduced balance and walking ability. Rehabilitation services are not readily available and the cost of delivering such programs remains high. Working with individuals with lower limb amputation, we created a virtual, peer-led physical activity behaviour change intervention called IMproving Physical Activity through Coaching and Technology following Lower Limb Loss (IMPACT-L3). We will conduct a pilot study to assess feasibility and optimize design of a future trial of effectiveness.

1.0 Introduction

1.1 Overview

Diabetes-related lower limb amputation (LLA) is a leading cause of disability globally.^1^ In the US alone, 185,000 LLAs are performed annually and the number of LLAs are projected to double by 2050 as a result of increasing rates of diabetes and the aging population.^2^ In Canada, 7,300 people have a LLA each year.^3^ More than 80% of these amputations result from complications of diabetes and/or peripheral vascular diseases (dysvascular LLAs).^3^ While dysvascular LLA commonly affects adults over age 65, there has been a resurgence of diabetes-related amputations in younger and middle-aged adults.^4^ LLA is a significant life event which impacts mobility, mental health and ultimately quality of life.^5-10^ In addition to disability resulting from LLA, individuals with dysvascular LLA often have multimorbidity (mean of five health conditions)^11 12^ and 37% of individuals require a contralateral or revision amputation within 5 years which can further impact their function and quality of life.^13^ Moreover, this population has a poor survival rate, estimated between 17 months and 4 years ^14-18^ with cardiovascular comorbidities cited as the leading cause of death.^18-25^ Due to their complex health challenges, people with dysvascular LLA have high rates of health care utilization (50% readmission rate)^26^ leading to high healthcare costs. While Canadian cost estimates are unavailable, healthcare costs for amputation in the US are >4.3 billion annually.^27^ With such high costs, rehabilitation services for people with LLA are often limited.^28 29^ In Canada, only 18% of adults with LLA receive inpatient rehabilitation and services are more available in urban than remote areas.^30^ These findings underscore the need for accessible, low-cost approaches to optimize health, social participation and quality of life in this population.

There is strong evidence that adequate physical activity reduces risk of chronic disease, all-cause and cardiovascular mortality and improves quality of life.^31^ Moreover, physical activity is a cornerstone of management of LLA^32^ and may confer additional benefits for people with dysvascular LLA such as improving diabetes outcomes and prevention and management of cardiovascular disease.^31 33^ Unfortunately, dysvascular LLA is characterized by high disability and low physical activity levels which may be a consequence of the amputation and comorbid conditions.^36^ ^39^ ^41^ People with dysvascular LLA have reduced strength, balance, cardiorespiratory fitness, walking ability and increased energy expenditure during ambulation.^35^ ^38^ ^53^ ^54^ Consequently, they have impaired mobility leading to sedentary behaviour. The presence of comorbidities and secondary conditions including skin problems (e.g., pressure ulcers)^55-58^ and musculoskeletal conditions (e.g., low back pain) can further impact individuals physical activity levels.^59^ Across studies examining physical activity in people with dysvascular LLA, step counts ranged from 1250 steps/day in older prosthesis users to 3809±2189 steps/day in people with diabetes-related LLA.^40^ ^60-62^ People with dysvascular LLA accumulated 24±41 minutes per week of moderate to vigorous physical activity, well below the minimum recommended 150 minutes per week.^40^ Importantly, not everyone with LLA can use a prosthesis due to muscle weakness, cognitive impairment or skin problems.^63^ ^64^ It can be difficult for wheelchair users to accrue adequate physical activity.^65^

Given the limited availability of rehabilitation services for LLA, accessible interventions to support physical activity in people with LLA are needed. Evidence suggests that multifaceted interventions that incorporate social support and behaviour change techniques increase physical activity in older adults and people with chronic illness.^34-37^ In a national meeting, stakeholders ranked research on peer led physical activity programs for people with dysvascular LLA as a top research priority.^38^ To date, no peer-led physical activity interventions for people with dysvascular LLA have been evaluated.^39 40^ To address this gap, we co-created a novel physical activity behaviour change intervention comprised of peer coaching, wearable technology and education. Prior to conducting a trial to determine effectiveness of the intervention, a pilot study is required to assess feasibility and optimize design of a future trial.

**1.2 Background**

***1.2.1 Barriers to Physical Activity***

A multitude of barriers can restrict physical activity participation in people with LLA. These barriers include lack of knowledge of physical activity, transportation to get to spaces to participate in physical activity, geographic features of the environment (e.g., stairs), co-morbid conditions, and availability of programs.^41^ ^68^ Consistently across studies, individuals with LLA identified support from others to engage in physical activity as important, including follow-up phone calls and counselling.^41^ In prior research, social support from peers with limb loss was perceived as a facilitator of physical activity.^69^ These findings underscore the need for supportive physical activity interventions that are accessible. Addressing factors known to optimize physical activity (e.g. self-efficacy, knowledge, motivation, social support) will be important to improve participation in physical activity after dysvascular LLA.^41^

***1.2.2 Effects of Physical Activity Interventions: Systematic Reviews and Recent Trials***

The physiological, psychological, and social benefits of physical activity are well established.^31^ Even minimal amounts of physical activity can improve functioning and slow the effects of deconditioning that are associated with disability.^41^ A systematic review and meta-analysis examined the effects of exercise programs on health in individuals with LLA, including data from 10 randomized controlled trials (with data up to 2019).^39^ Overall, combined exercise programs (e.g., strength, balance, aerobic training) had positive effects on distance walked, cardiorespiratory fitness, muscle strength and function. However, **only four of the 10 studies included people with dysvascular LLA**.^42-45^ A more recent systematic review found that exercise performed one to three times per week improved balance, walking speed, walking endurance and transfer ability in adults with LLA, especially when combining aerobic exercises with lower limb strengthening or balance exercises.^46^ Similarly, few individuals with dysvascular LLA were included in the studies (35%).^46^ Two of the studies focused on behaviour change. One study was a pilot RCT, which examined the preliminary efficacy of a physical activity intervention in people with dysvascular LLA.^42^ The intervention included weekly 30-minute telephone sessions with a therapist for 12 weeks focused on health behavior change. Step count increased 1135 steps per day in the intervention group compared to 144 steps per day in the control group (P=.03). However, the sample was recruited from 3 hospitals and the sample was predominantly male (3/38 females) limiting generalizability of the findings. A similar feasibility study of a biobehavioral intervention including 12 video sessions delivered by a therapist to support physical activity behaviour change, established the feasibility of the intervention (90% retention rate, low safety risk).^47^ The study was limited by a small sample size of male veterans from one centre. To our knowledge, no studies have assessed a peer-led physical activity behaviour change intervention for people with dysvascular LLA.

***1.2.3 Co-Creation of a Physical Activity Behaviour Change Intervention***

In 2020, stakeholders (i.e., people with LLA, clinicians, researchers and community agencies) from across Canada identified research priorities on physical activity for people with LLA.^47^ Lack of opportunities for peer support for adults with dysvascular LLA was the second highest ranking issue. To advance a solution, participants outlined a plan to develop and evaluate an evidence-based physical activity program using trained peers. In addition, our team conducted a qualitative study exploring physical activity in people with LLA.^69^ Barriers to physical activity included access to physical activity programs for people with LLA (i.e., lack of availability, physical accessibility, and transportation). Social support from peers who provide encouragement and accountability was perceived to facilitate participation in physical activity.^69^ Building on this research and using prior literature and theory, our team of researchers, clinicians and people with LLA designed a physical activity behaviour change intervention: **IM**proving **P**hysical **A**ctivity through **C**oaching and **T**echnology following **L**ower **L**imb **L**oss (**IMPACT-L3**). A logic model for the intervention can be found in Appendix A.

**2.0 Study Objectives**

The **primary aim** is to assess the feasibility of conducting a randomized controlled trial to determine the effectiveness of a virtual peer-led physical activity intervention on levels of physical activity and self-efficacy compared to a wait-list control in people with dysvascular LLA.

**Specific objectives** are to:

1. Evaluate feasibility according to indicators of process, resources, management and treatment.
2. Explore perceptions of program characteristics, program implementation and study procedures among individuals with LLA; and
3. Explore the perceived feasibility and acceptability of the program among peer coaches.
4. Inform a sample size calculation for a future trial of effectiveness.
5. Assess construct validity of physical activity and self-efficacy measures among individuals with dysvascular LLA.

3.0 Methods

3.1 Study Design

This pilot study is a parallel group RCT with an embedded qualitative component. A pilot study is a subset of feasibility studies which asks questions about feasibility (whether the future trial can be done and, if so, how) but with a key design feature: in the pilot study, the future RCT is conducted on a smaller scale. Prospective recruitment, concealed group allocation, evaluator masked outcome evaluation and waitlist control will be employed. The research is guided by the MRC framework for evaluating complex interventions.^51^ We will follow the extension to the Consolidated Standards of Reporting Trials Statement for reporting pilot and feasibility RCTs.^87^

3.2 Participants

Individuals who meet the following inclusion criteria will be included: 1) Dysvascular LLA (LLA due to diabetes or vascular disease); 2) major LLA (at the ankle or above); 3) living in the community; 4) adult at least 18 years of age; 5)comfortable communicating in English and **a**ble to understand basic English; and 6) receptive to using a phone or tablet (e.g., to enable peer coaching, access to modules. Participants may be ambulatory with a prosthesis and/or use a wheelchair.

Exclusion criteria include: 1) actively receiving rehabilitation services related to physical activity/mobility; 2) recommended medical supervision for physical activity by health care provider, ^102^ or skin problems preventing usual activity and 3) not able to provide informed consent.

Participants who are interested in taking part in the study but who do not have access to a device will be offered the use of a device to borrow. The number of participants who may be offered the use of a device may be limited. Participants who may require additional support with the use of technology will be provided such supports to increase accessibility. This support may include instructions and support with accessing and signing in to Zoom/WebEx/Teams and walking through the use of Zoom/WebEx/Teams to facilitate peer coaching sessions and/or accessing and walking through the online modules and/or study measures.

**3.3 Experimental Intervention (IMPACT-L3)**

Theory-based interventions are more effective in increasing physical activity.^48^ Two theories provide a framework for IMPACT-L3. One is social cognitive theory, which is a useful theoretical lens for incorporating self-efficacy into interventions.^49 50^ Self-efficacy is the belief a person has in his or her ability to perform a behavior successfully.^51^ Self-efficacy is informed by skill mastery, vicarious experience, verbal persuasion, and reinterpretation of physiological and affective symptoms.^51^ The other is self-determination theory, which provides a framework for cultivating an autonomy-supportive social environment that promotes behavior change.^52^ This is achieved by satisfying three basic psychological needs of autonomy (i.e., volition in one’s own behavior), competence (i.e., interacting effectively with one’s environment by mastering tasks), and relatedness (i.e., sense of belonging).^52^ These constructs were integrated into IMPACT-L3. As eHealth solutions have the potential to increase access and improve health outcomes,^53 54^ IMPACT-L3 will be delivered entirely virtually.

Peer health coaching (~30 minutes weekly) will be delivered by a peer trainer over 8 weeks. Peer trainers, who have experienced a dysvascular LLA themselves, will be matched to a participant based on gender and level of amputation to promote a sense of understanding and belonging. Individuals with higher level amputations (i.e., above knee) are less physically active and face more challenges with mobility (e.g., greater energy expenditure)^55 56^ and may benefit from a peer with similar experience. Peers will be trained to implement the intervention including specialized training in brief action planning (BAP), a structured support technique grounded in the principals and practices of motivational interviewing (Appendix C). Training will be delivered by an organization which provides certified training in BAP ([Centre for Collaboration, Motivation and Innovation](https://ccmi.learnupon.com/store/300131-brief-action-planning-certification))^57^ including an online course and practice and feedback. The trained peer will help participants **set goals and create an action plan for physical activity** that they feel confident that they can achieve. During weekly meetings, peers will help participants problem solve challenges to physical activity and overcome barriers. The peer trainer will deliver the intervention through **voice or video calls** (depending on preference). Video calls will be preferred because “face-to-face” interactions may reinforce vicarious experiences (e.g., peers demonstrate movements). Peers will complete a standardized form at every interaction to review goals, goal progression (e.g., Apple Watch data), action plans, and document barriers/facilitators. Peer health coaches will be asked to complete a standard form for each coaching session (Appendix D). Weekly debriefings among peers and the research team will problem solve challenges and monitor peer burden.

To improve competence and skills to enhance physical activity, participants will have access to five web-based modules developed based on qualitative interviews and co-design workshops with people with LLA. Modules include content on physical activity including benefits of physical activity, types of physical activity (strengthening, aerobic, balance, flexibility), intensity of activity (light, moderate, vigorous), exercise safety and limb management to enable physical activity, and recommended physical activity. The written materials that correspond with the online modules is included in Appendix E. The modules will be housed on a learning management system at the University of Toronto. They will include videos. Participants will be given a login and will be asked to review modules at their own pace each week for the first 5 weeks.

To support behaviour change, participants will be provided with a wearable to track their physical activity: an Apple Watch to be worn at the wrist of the non-dominant side. An off the shelf wearable was selected for the study **to optimize sustainability of the intervention in a real-world setting**. Apple Watch has been shown to be accurate in tracking step count in a subgroup of populations^58^ and can measure wheelchair pushing thus making it the best option available.^59^ Participants will be trained to wear and use the Apple Watch 24 hours a day during the intervention time only, including water-based activity. Wearables that provide personalized, and actionable feedback promote better behavior change outcomes.^60^  Data from the Apple Watch will be shared verbally with the peer during discussions between participants and peers during the weekly virtual sessions to facilitate behaviour change.

**Control:** The control group will continue with their usual health care and be offered the intervention program at the end of the follow-up period (wait-list control).

**3.4 Outcome Measures**

Data will be collected at baseline, week 9 and a short follow-up 4 weeks later (3 months).

**3.4.1 Feasibility Measures**

The primary outcome of this study is feasibility of implementing the intervention and conducting the trial. Feasibility indicators will be collected including assessment of process, resource, management and treatment indicators (Appendix D).

**Process Indicators:**

*Recruitment rate* will be evaluated by the number and proportion of participants recruited per month and the number and proportion of peers recruited.

*Consent rate* will be calculated as the percent of recruited individuals who provide consent per month.

*Withdrawal rate* will be calculated as the percent of study participants withdrawing by week 9 (T2) and 3 months (T3).

*Acceptability* will be assessed in qualitative interviews and by the theoretical framework of acceptability (TFA),^103^ a brief questionnaire developed to assess acceptability in the design, evaluation and implementation of interventions.

**Resource Indicators:**

*Participant adherence* will be measured as the percentage of peer coaching sessions participants attend. Participants’ usage of web-based modules will be measured (i.e., number of completed modules, number of logins).

*Peer coach adherence* will be assessed by tracking the total number of peer coaching sessions attended by the peer-trainer.

*Participant and tester burden* will be measured by the amount of time it took to administer study outcomes at T1, T2, and T3 and the acceptability of the evaluation time commitment from the perspective of participants.

*Feasibility of data collection* will be evaluated as the percentage of participants with complete data on each measure at each evaluation time point. For accelerometers, the percentage of devices that were returned at baseline and follow-up (9 weeks, 3 months) and the amount of valid wear time will be assessed.

**Management Indicators:**

*Participant processing time* will be assessed as time from initial contact to enrolment.

*Intervention fidelity* will focus on adherent and competent delivery of the intervention. It will be evaluated using the study-specific checklist outlining key components of the intervention completed by peers. A subset of peer coaching sessions (at least one per dyad) will be recorded and reviewed by research staff using the checklist.

**Treatment Indicators**:

*Adverse events* will be measured as the number of adverse events that occurred during physical activity for the intervention. Adverse events (e.g., falls) will be documented by peers on the standardized form used at each coaching session.

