**3.17 Benefits and Risks**

There are **minimal** additional risks to participants in the study, **which are inherent to physical activity participation**. However, the long-term benefits outweigh those risks. Telephone-based physical activity interventions have been shown to be safe for people with dysvascular LLA in RCTs. To enhance safety with physical activity (e.g. reduce risk of falls, skin problems), LLA-specific education modules will address exercise safety and peers will be trained in how to address risks.

During interviews, some participants may feel uncomfortable answering questions about their health. All participants will be informed they are not required to respond and may “pass” any questions they do not wish to address.

While the risk is low, participants could experience distress, for example, while completing assessments. If any participants exhibit signs of distress while completing the assessments, the research team will follow up with those participants and if needed, provide them with a list of mental health resources (Appendix I).

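### Adverse events are recorded only through intervention-arm coaching, so the pilot gets an incomplete count and no comparison between arms

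*Protocol*

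**What the plan says.** Adverse events are the only treatment indicator in section 3.4.1, which sets out the primary feasibility outcome. The indicator "will be measured as the number of adverse events that occurred during physical activity for the intervention". On the source, the events "will be documented by peers on the standardized form used at each coaching session".

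Section 3.3 says when that form is filled in ("Peers will complete a standardized form at every interaction to review goals, goal progression") and for how long coaching runs: "Peer health coaching (~30 minutes weekly) will be delivered by a peer trainer over 8 weeks". For the comparator it says: "The control group will continue with their usual health care and be offered the intervention program at the end of the follow-up period". Section 3.4 gives the assessment times: "Data will be collected at baseline, week 9 and a short follow-up 4 weeks later (3 months".

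The withdrawal rate "will be calculated as the percent of study participants withdrawing by week 9 (T2) and 3 months (T3", and no recording of reasons is mentioned. Section 3.17 names the risks that the education modules and peer training are meant to reduce: "To enhance safety with physical activity (e.g. reduce risk of falls, skin problems".

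Section 3.11 (Objective 1) says that the indicators feed a red/amber/green judgement on progression, with details in Appendix D, which is not available here.

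**The concern.** The protocol fixes both what counts as an adverse event and who records it. Both choices tie capture to contact between an intervention participant and a peer coach. Where there is no such contact, the text gives no route for recording an event. That applies to the whole control arm, to the weeks after coaching, and to anyone who stops seeing the peer.

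Two things are at stake. First, under-recording works in one direction: fewer recorded events make the treatment indicator look better when progression is discussed. Second, section 3.1 describes a pilot as the future trial run on a smaller scale. A procedure for collecting harms in both arms is something such a pilot should try out, and this one would hand the main trial no control-arm information.

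**Working it through.** The protocol states no safety figure, so there is nothing to reproduce. The check sets the rule against the design and then works out how much follow-up it covers.

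**Inputs**
- Coaching: 8 weekly sessions (section 3.3).
- Last assessment: week 9 plus 4 weeks, also called 3 months (section 3.4). This is 13 weeks by the first description and about 12 if 3 months is read as 12 weeks.
- Planned size: 30 per arm, allowing 20% dropout (section 3.5).
- Assumptions: coaching starts straight after baseline, arms are equal, everyone is followed to the last assessment, and each form covers the whole time since the previous session.

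**1. Control arm.** Controls have no peer until follow-up ends, so no form is completed for them. Coverage is 0 weeks. The words *for the intervention* may mean activity done as part of the programme or events in the intervention group; controls are left out on either reading.

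**2. Intervention arm.**
- Coverage: 8/13 = 62%, or 8/12 = 67%.
- Uncovered time up to week 13: 13 − 8 = 5 weeks from the end of coaching, or 13 − 9 = 4 weeks from the week-9 assessment. That is 5/13 = 38% or 4/13 = 31% of follow-up.

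**3. Both arms together.** Share of randomised person-time with any capture: 8/(2 × 13) = 31%, or 8/(2 × 12) = 33%. This is a best case, because it supposes that every session is held.

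**4. Participants who leave.** The dropout allowance is 0.20 × 30 = 6 per arm. The documents do not say how many would leave because of an event. An intervention participant who does, and has no later contact with the peer, appears only in the withdrawal percentage.

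**5. Definition.** Section 3.17 names skin problems as a risk, section 1.1 lists pressure ulcers among secondary conditions, and section 3.2 excludes people whose skin problems prevent usual activity. A skin problem need not arise or be noticed during activity, so a harm that the protocol screens for at entry may not count if it develops later.

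**6. Direction of the error.** If E events meet the definition and a share q goes unrecorded, the expected count is E × (1 − q), which cannot exceed E. The error can only lower the count. The documents give neither E nor q, so its size cannot be stated.

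**The case against.** The best defence is that the pilot does not set out to compare safety. The objectives in section 2.0 concern feasibility, perceptions, sample-size input and construct validity, and the Objective 1 analysis is descriptive. Counting only activity-related events is then a narrow choice, not a contradiction. Section 3.11 also warns against weighing one indicator alone. This stands, and it is why the point is a recommendation.

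Several stronger readings are tempting but not supported:
- *The pilot cannot judge safety at all.* Activity-related events reported to coaches can still be described.
- *The control arm would show a false zero.* No control count is defined, so none would be reported.
- *A missed session loses the event.* Coaching is by voice or video and the form is completed at every interaction, so an event can be reported next time. It is lost only when contact ends.
- *The rule is what prevents the pilot from showing excess harm.* Size limits that anyway. With full capture and assumed rates of 20% and 40%, 30 per arm gives about 39% power and a 95% interval half-width of 1.96 × √(0.2 × 0.8/30 + 0.4 × 0.6/30) = 23 percentage points. Likewise, the wide upper limit after zero events in 30 reflects sample size and would not change with better capture. An assumed background fall rate does not measure the defect either.

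Other routes exist but do not replace capture. Self-reported healthcare use (section 3.4.3) is a descriptive variable limited to the intervention period, and a fall or skin problem need not lead to care. The weekly debriefings (section 3.3) depend on the same peers. The interviews (section 3.10) sample about 15 to 20 participants and explore experience of the programme and study procedures. Appendix D may hold more, so the finding is limited to the protocol text.

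**Conclusion.** The concern holds in a limited form. As the protocol text stands, adverse-event capture covers one arm, for 8 of about 12 to 13 weeks, through one reporter, with a definition that may leave out skin problems. The result is a usable description of activity-related events reported to coaches. It is neither a complete count nor a comparison between arms, and any error makes the indicator look more favourable.

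The 31 to 33% coverage figure rests on the timing assumptions listed above. The conclusion on direction also assumes that fewer events count in favour of progression, since the progression table is not shown. No objective, allocation procedure or planned analysis is invalidated. This is a cheap improvement worth making before enrolment proceeds, because events not asked about at the time are hard to recover.

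**What to change.** - Add identical short adverse-event items (falls, residual-limb or skin problems, other events) to the self-completed REDCap questionnaires at week 9 and 3 months in both arms, covering the period since the last assessment.
- Ask the same items at withdrawal where the participant can be reached.
- Keep the peer form as an additional source in the intervention arm.
- Report events descriptively by arm, and use occurrence during physical activity as a sub-classification instead of the definition.

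The cost is a few minutes of participant time at two assessments that already take place. There is also a small risk to masking: section 3.9 has one masked assessor collecting all data, and answers about activity or coaching could reveal allocation. Keeping the items self-completed and out of that assessor's view limits this. Section 3.4.4 already provides for self-completion, with staff on hand for technical problems.
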